## Abstract

**Background:**

Children with disability face long wait times for rehabilitation services. Before the COVID-19 pandemic, telehealth adoption was low across pediatric rehabilitation. Owing to the COVID-19 pandemic restrictions, pediatric therapists were asked to rapidly shift to telehealth, often with minimal training. To facilitate the behavior changes necessary for telehealth adoption, provision of appropriate evidence-based training and support is required. However, evidence to support the effective implementation of such training is lacking. The successful real-world implementation of a training intervention and program of support (TIPS) targeting pediatric therapists to enhance the adoption of family-centered telerehabilitation (FCT) requires the evaluation of both implementation and effectiveness.

**Objective:**

This study aimed to evaluate TIPS implementation in different pediatric rehabilitation settings and assess TIPS effectiveness, as it relates to therapists’ adoption, service wait times, families’ perception of service quality, and costs.

**Methods:**

This 4-year, pan-Canadian study involves managers, pediatric occupational therapists, physiotherapists, speech-language pathologists, and families from 20 sites in 8 provincial jurisdictions. It will use a multimethod, prospective, hybrid type 3 implementation-effectiveness design. An interrupted time series will assess TIPS implementation. TIPS will comprise a 1-month training intervention with self-paced learning modules and a webinar, followed by an 11-month support program, including monthly site meetings and access to a virtual community of practice. Longitudinal mixed modeling will be used to analyze indicators of therapists’ adoption of and fidelity to FCT collected at 10 time points. To identify barriers and facilitators to adoption and fidelity, qualitative data will be collected during implementation and analyzed using a deductive-inductive thematic approach. To evaluate effectiveness, a quasi-experimental pretest-posttest design will use questionnaires to evaluate TIPS effectiveness at service, therapist, and family levels. Generalized linear mixed effects models will be used in data analysis. Manager, therapist, and family interviews will be conducted after implementation and analyzed using reflective thematic analysis. Finally, cost data will be gathered to calculate public system and societal costs.

**Results:**

Ethics approval has been obtained from 2 jurisdictions (February 2022 and July 2022); approval is pending in the others. In total, 20 sites have been recruited, and data collection is anticipated to start in September 2022 and is projected to be completed by September 2024. Data analysis will occur concurrently with data collection, with results disseminated throughout the study period.

**Conclusions:**

This study will generate knowledge about the effectiveness of TIPS targeting pediatric therapists to enhance FCT adoption in pediatric rehabilitation settings, identify facilitators for and barriers to adoption, and document the impact of telehealth adoption on therapists, services, and families. The study knowledge gained will refine the training intervention, enhance intervention uptake, and support the integration of telehealth as a consistent pediatric rehabilitation service option for families of children with disabilities.

**Trial Registration:**

ClinicalTrials.gov NCT05312827; https://clinicaltrials.gov/ct2/show/NCT05312827

**International Registered Report Identifier (IRRID):**

PRR1-10.2196/40218

## Introduction

### Background

Timely access to family-centered services for children with disabilities and their families is crucial for supporting their development and well-being [1-3]. Currently, many children face long wait times (ie, up to 2 years) as well as organizational, geographic, or cultural barriers to services [4-6]. Lack of service access can lead to negative developmental, health, and social consequences for children and their families [7-10]. The COVID-19 pandemic further exacerbated these issues, as rehabilitation support for children was significantly reduced [11], increasing parental mental health burden (eg, stress and depression) [7-10]. To minimize the negative impacts of these service disruptions, therapists shifted to telehealth service delivery [7,9,12,13].

Telehealth is defined as any asynchronous or real-time clinical intervention provided remotely by clinicians (in this case, therapists) to patients or caregivers [14-16]. Telehealth is an important alternative for families living in underserved or remote areas [14,17-21]. However, some families in well-served urban locations also prefer the convenience of telehealth over in-person visits for reasons such as decreased travel time and schedule flexibility [15,16]. Before the COVID-19 pandemic, a systematic review of randomized controlled trials of pediatric rehabilitation delivered via telehealth supported the efficacy of rehabilitation provided via telehealth for diverse populations and a wide range of effects, including improved service access, child outcomes (eg, behavior), and family satisfaction [22]. Telehealth interventions have yielded promising results [23,24], and the acceptability [17,25-28] of telehealth has been previously established, further supporting its integration into comprehensive family-centered services [17,27,29,30].

Despite its established efficacy, the adoption of telehealth is low across rehabilitation, including in pediatric patients. An international survey conducted in August 2019 involving 1133 pediatric therapists from 76 countries reported that 3.9% of the pediatric therapists were using telehealth. However, in a follow-up survey completed in May 2020 (ie, during the public health restrictions imposed by the COVID-19 pandemic) with a subsample, 70.1% of the pediatric therapists had adopted telehealth. Many reported doing so without prior experience and lacked confidence, knowledge, and training in effective intervention strategies [12]. When asked about the support required to implement telehealth, training was by far the most frequently cited, and elements of training considered important included communication skills with families over the telephone and internet, safe and effective use of platforms, reliable assessment tools and processes, and intervention strategies for children of various ages and health conditions [12]. Although therapists’ knowledge, skills, and attitudes toward telehealth can improve with time and experience [31], training and support are required for behavioral changes to occur [32-34]. Unfortunately, there is a paucity of evidence on how personal and contextual factors may influence telehealth training and support [35]. Targeting therapists’ knowledge, skills, and attitudes associated with their intention to adopt telehealth and their role within family-centered services appears vital to the effective implementation of telehealth [35-43].

Family-centered telerehabilitation (FCT) is defined as pediatric rehabilitation that uses family-centered care practices while working with families remotely. Family-centered care is recognized as the best practice approach in pediatric rehabilitation [44]. Described as a partnership approach, family-centered care is based on the belief that the child’s well-being and care needs are best supported within the family context through effective family-provider collaborations [45]. A central family-centered care tenet is the assumption that the processes of care delivery are as important to child and family outcomes as the specific characteristics of the clinical intervention delivered [45]. Family-centered care is characterized by practices that promote clinical flexibility; respect and dignity for families’ perspectives, knowledge, strengths, and characteristics; effective information sharing (general and specific), partnership, and collaboration among parties to support decision-making; and coordinated and comprehensive care delivery [30]. Furthermore, family-centered care occurs in therapeutic environments that optimize the development of family-provider partnerships [46-49], in which parents are active participants in collaborative goal-setting therapy [50,51], planning, implementation, and evaluation [44,46,52,53] and where activities are integrated within daily routines and contexts such as home and community [54].

Telehealth offers additional opportunities to enhance family-centered care practices [30,55] as it provides convenient and flexible ways to partner with families, respecting individual family composition, characteristics, and constraints (eg, geographical, temporal, and financial) [21]. Furthermore, it allows real-time knowledge acquisition and information sharing about the child within their contexts and supports family decision-making and parents’ psychosocial well-being such as decreased anxiety, stress, and depression [21]. Finally, telehealth has been recognized as an important addition to comprehensive care coordination and service delivery [56].

As a result of the pandemic, considerable momentum exists to support the uptake of FCT and foster its ongoing sustainable use within accessible and supportive services for the families of children with disabilities. Pediatric rehabilitation therapists, service managers, professional associations, policy makers, and patients are calling for resistance to *returning to normal* and instead are requesting help to sustain telehealth as part of the FCT continuum of care [28,29,56,57]. For this shift to occur, therapists require tools, training, and support. The proposed study aims to evaluate the implementation of a training intervention and program of support (TIPS) to enhance the adoption of FCT in pediatric rehabilitation centers across Canada and to assess its impact on wait times, families’ perception of service quality, and costs.

### Intervention

TIPS is an evidence-informed, multifaceted intervention, informed by empirical evidence in the field of pediatric rehabilitation and effective implementation strategies [16,58-62]. TIPS consists of the following components: (1) a 10-hour intensive training program offered to participating therapists at each site over a 1-month period, which includes 4 hours of self-paced learning modules and a 6-hour mandatory webinar and (2) an 11-month program of support composed of monthly mentoring meetings at each site led by the local therapist champion and a national, virtual community of practice. The virtual community of practice will be offered simultaneously to all participating therapists across Canada and facilitated by 3 national knowledge brokers—an occupational therapist, a physiotherapist, and a speech and language pathologist—experienced in FCT in pediatric rehabilitation. Figure 1 illustrates components and time frame of TIPS.

**Figure 1 figure1:**

Training intervention and program of support description. FCT: family-centered telerehabilitation; KB: knowledge broker; vCoP: virtual community of practice.

The TIPS self-paced learning modules are informed by contemporary family-centered care frameworks and the family-oriented service continuum [30]. More specifically, they will address FCT core components and provide practice examples. Modules will address the following topics, as they apply to telehealth: (1) overview of family-centered care premises and principles (eg, information provision; respectful, supportive, and comprehensive care; and enabling partnerships) [63,64], (2) parent-professional collaborative partnerships (eg, goal cocreation, parent and child engagement, and role negotiation) and helpful FCT instruments and strategies [65], (3) coaching in the FCT context (eg, various approaches and strategies) [52,66], and (4) factors influencing service delivery model choice (ie, face-to-face or telehealth) [12]. As per best practice [16] and using education course creation software, several members of the study team will codevelop multimedia content (eg, videos and presentations) for the asynchronous training in consultation with pediatric clinicians and other experts (eg, parent partners, national organizational partners, inclusion and diversity experts, and knowledge keepers). We will upload the curriculum to a password-protected web-based platform for which a unique username and password will be required. Knowledge acquisition, based on specified learning objectives and key messages targeted in each training module, will be assessed through short quizzes. Completion of the asynchronous modular training and knowledge assessment will be recommended before undertaking the synchronous webinar.

A 6-hour synchronous webinar component will also be delivered to participants by members of the research team and 3 knowledge brokers. The webinars will engage therapists in discussions using case studies and interactive activities (eg, role play, vignettes, and simulations) to build their critical thinking on how to implement these practices in their context and with the families they serve. The webinar content will be adapted for each site in consultation with the local leadership team (ie, a site manager, a therapist champion, and a parent or patient partner). This coadaptation phase will ensure that activities and practice examples are tailored to individual site contexts and processes (eg, engagement practices, site clinical goal-setting processes, and service coordination as per team procedures) and that webinars are learner-centered and clinically relevant. Therapists will be encouraged to consider various asynchronous and real-time technologies, including email, telephone, web-based platforms, and videoconferencing systems that best respond to families’ needs and preferences and are approved by their organizations. The research team will refrain from recommending specific technologies. There will be no prescribed frequency or duration for the FCT interventions; rather, therapist participants will work with families according to their goals and preferences, and site-specific organizational policies.

Finally, a program of support will be offered for the remaining year via monthly videoconference mentoring meetings and access to the virtual community of practice, which will be housed on the password-protected web-based platform. Monthly meetings will focus on sharing site-specific successes and challenges, proposing solutions and reporting results, as well as sharing practical evidence-informed resources. The evidence-informed virtual community of practice, facilitated by the 3 national knowledge brokers, will be used to canvas for solutions to address challenges at a national level; share successes; discuss specific cases for guidance, feedback, and input; and share useful tips, tricks, and resources [43,59,67-71].

### Research Question and Study Objectives

Our hybrid implementation-effectiveness study examining the implementation of TIPS aims to answer the following research question: *Can TIPS enhance the adoption of FCT interventions by therapists working in different contexts?*

Specific objectives of the study include the following:

Implementation evaluation primary objectives: to assess therapists’ intention to adopt FCT practices and evaluate therapists’ fidelity to FCT practicesImplementation evaluation secondary objectives: to document the contextual variations required to coadapt TIPS to meet each site’s needs and identify factors influencing FCT adoption and fidelity

For the implementation evaluation, we hypothesize that, in the short term (ie, 1 month after TIPS), therapists’ intention to adopt FCT will increase minimally and their fidelity to FCT practices will improve minimally. After the implementation of TIPS (ie, >1 month), we expect that FCT adoption will increase and the fidelity of FCT practices will improve modestly. We also expect that engagement will fluctuate over time, across sites and therapists and will depend on therapist, client, organizational, and system factors.

Effectiveness evaluation: to compare service wait times, families’ perceptions of service quality, and changes in service delivery before and after the implementation of TIPS and explore the costs (and cost savings) related to increased use of FCT

For the effectiveness evaluation, we hypothesize that for sites with the largest effect change in intention to adopt FCT and the fidelity of FCT practices, (1) wait times will significantly decrease and (2) families’ perceptions of service quality will significantly improve after the implementation of TIPS. In relation to cost, we also expect families to experience cost savings after the implementation of TIPS and managers to report no additional costs incurred because of TIPS.

## Methods

### Study Design

The TIPS study is a 4-year, multimethod, hybrid type 3 implementation-effectiveness trial, registered with ClinicalTrials.gov (NCT05312827). Hybrid implementation-effectiveness trial designs are recommended when the traditional research pipeline of efficacy-effectiveness-implementation is too time-consuming and considered unethical, failing to adequately respond to the urgency of the expressed need [72]. TIPS is well suited to this type of hybrid implementation-effectiveness design because (1) there is momentum for its implementation within the health care system, (2) minimal risk is associated with the clinical intervention and the implementation strategy to support generalizability, (3) there is strong face validity and indirect evidence for the clinical intervention and implementation strategy to support generalizability, and (4) there is evidence of feasibility for the implementation strategy and support in the clinical and organizational context under study [72]. A prospective, hybrid type 3 design reflects a collaborative ethos because it allows end users to inform the refinement and improvement of clinical interventions and their implementation processes [72,73]. Implementation strategies will be adjusted during the intervention refinement process in consultation with parents of children with a disability, clinicians supporting these families, individuals with experience implementing digital health, including health services managers, as well as the pediatric rehabilitation implementation sciences literature. Potential additional user-identified strategies will be integrated as part of the consultation process and according to the collaborative approach adopted. These strategies may allow previously unrecognized FCT implementation barriers to be acknowledged and addressed.

### Study Settings

Participating sites are publicly funded organizations providing outpatient pediatric rehabilitation or child development services to children aged 0 to 12 years with, or at risk of, disability. *Disability* is used inclusively to recognize all medical diagnoses associated with limitations in functioning, such as cerebral palsy and autism spectrum disorder. The term *at risk* includes children presenting with delayed development who may not yet have a diagnosis but who experience functional limitations and qualify for rehabilitation services. The upper age limit of 12 years was chosen, as best practices regarding transition of care suggest that different relationships should be fostered with adolescents aged >12 years [74].

The 20 participating sites were selected to be representative based on various characteristics (eg, population, size, services provided, catchment area, and geography) posited to influence outcomes, the effects of which will be explored. These sites are clustered into 6 regions (one of which includes 3 provinces with a single participating site). To limit the risk of contamination, and as per the interrupted time series design, TIPS will be implemented in all sites in the same region during the same month and sequentially introduced across all regions, 2 months apart. Training will be conducted on a site-by-site basis to create team cohesion. The 2-month implementation interval between regions provides flexibility for organizing implementation and data collection activities.

### Participants

Participants will be recruited from study sites according to the following eligibility criteria:

Managers (n=20; one per site): managers, or their delegates, responsible for rehabilitation services at the site and members of the local leadership team, will participate in the coadaptation of TIPS to their site. Managers may contribute to their site’s monthly mentoring meetings; aid in the recruitment of therapists, parents, a therapist champion, and a parent-partner for their site; and complete site- or service-specific data collection instruments before and after the implementation of TIPS.Therapists (n=600 with 50% anticipated response; n=300): physiotherapists, occupational therapists, or speech-language pathologists providing outpatient pediatric rehabilitation services to children aged 0 to 12 years at each site are recruited via the managers and are interested in using FCT. Therapists will participate in the TIPS program, complete data collection instruments as prescribed, and aid in parent recruitment.Parents (n=20 per therapist with an anticipated response rate of 33%; n=2000 families per assessment time point): 1-time data collection will be undertaken with 2 samples (preimplementation and postimplementation samples) of parents or caregivers who received services (either in-person, virtually, or both) from at least one participating therapist in the previous 3 months.Therapist champion (n=20; one per site): a therapist selected based on their telehealth experience and on peer recognition within their organization. Therapist champions are members of the local leadership team participating in the coadaptation of TIPS to their site and will oversee the monthly mentoring meetings and agree to report on the implementation process after the implementation of TIPS.Parent or patient partner (n=20; one per site): parent or patient partners will primarily be recruited from family, parent, or patient advisory committees at the participating sites or, in the absence of such initiatives, from regional, provincial, or national patient engagement programs. As members of the local leadership team, parent or patient partners will participate in the coadaptation of TIPS to their site and could be called upon to contribute to their site’s monthly mentoring meetings.

Recruitment procedures will be flexible and will be adapted to the preferences, policies, and procedures at each site. The recruitment of participants may be undertaken by email and sent directly to the potential participant by the research team (eg, therapists) or by the manager or therapist on behalf of the research team (eg, parents).

### Sample Size

#### Number of Sites

A total of 20 sites across 8 Canadian provinces (grouped into 6 regions for the intervention rollout) are included in the study. Whenever possible, at least 3 sites per province were included to ensure sample diversity, enable the exploration of the provincial health systems’ effects on the outcomes, and estimate site-related variations in outcomes. A total of 5 regions will include sites in the same province, whereas 1 region will consist of sites from 3 different provinces where only 1 rehabilitation program is available.

#### Number of Therapists

At the therapist level, implementation outcomes will be assessed 3 times during each period (before, during, and after the implementation of TIPS) for a total of 10 data collection time points. Assuming an autocorrelation of repeated measures of *r*<0.3, data collected from 300 therapists will provide >80% power to detect moderate effect sizes (Cohen *d*≥0.5), using a first-order autoregressive segmented regression model [75] and a global type I error level of 5%, accounting for multiplicity of outcome assessments (Šidák correction) [76].

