#### Data Analysis

To evaluate implementation (ie, objective 1), longitudinal mixed modeling accounting for and considering potential methodological issues associated with an interrupted time series analysis (eg, autocorrelation and time-varying confounders) will be used to analyze implementation indicators (ie*,* Assessment of Competencies and Contributors to Enhance Practice Transition to Virtual Family Centered Care survey, therapists’ self-reported FCT frequency, FCT fidelity self-perceived checklist, and PRIME-SP). Changes will be documented in the short term (ie, 1 month after TIPS introduction) and in the long term (ie, at the end of TIPS, 12 months after its introduction). Models will be covariate-adjusted to reduce potential confounding bias, including the therapists’ characteristics (eg, gender and years of experience) and site characteristics (eg, service provided, geography, and general patient characteristics), to estimate associations of key explanatory variables alongside TIPS. Secondary analyses will explore the heterogeneity in changes of outcome measures across genders, sites, therapists, and health jurisdiction levels.

*Secondary implementation objectives* will be evaluated using a multimethod approach.

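### Optional improvement: step-down Holm-Šidák would hold the same global 5% for the therapist outcomes as the named Šidák correction and never reject less

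*Protocol article*

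**What the plan says.** The multiplicity method for the therapist outcomes appears in the sample-size section of the protocol article, under Number of Therapists: "a global type I error level of 5%, accounting for multiplicity of outcome assessments (Šidák correction"). The same sentence says that "data collected from 300 therapists will provide >80% power to detect moderate effect sizes" (Cohen d of 0.5 or more), with an autocorrelation below 0.3 and a "first-order autoregressive segmented regression model".

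The Data Analysis section of the implementation evaluation lists four indicators: the ACCEPT-VFCC survey, then "therapists’ self-reported FCT frequency, FCT fidelity self-perceived checklist, and PRIME-SP". It names no multiplicity rule. The only other use of Šidák is in the effectiveness evaluation, where intervention effects are to be reported with Šidák-corrected 95% intervals. No step-down procedure is named anywhere.

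On the size of change, Research Question and Study Objectives expects that one month after TIPS "therapists’ intention to adopt FCT will increase minimally and their fidelity to FCT practices will improve minimally", with modest improvement in fidelity later. Neither word is given a number.

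**The concern.** Single-step Šidák holds every outcome to the strictest level, however many of the others are already clearly significant. The step-down version starts at that level and relaxes after each rejection, while keeping the same family-wise error. So the named method gives up some power and gains nothing in control of the family-wise error.

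This could matter because the power statement covers only d of 0.5 or more, while the authors predict minimal to modest change. The four indicators are reported by the same therapists and may well move together, and it is when several effects are real that step-down helps. At stake is whether a second, third or fourth real change is declared significant.

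**Working it through.** **Inputs from the article.** 300 therapists; autocorrelation up to 0.3; global 5%; assessments at months −3, −2, −1, 0, 1, 4, 8, 12, 15 and 18.

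**Assumptions, because the article does not give them.** Family size m=4 (the four listed indicators), with 2 and 8 as alternatives; equal effects; correlation 0.5 between outcomes; two-sided normal tests; complete data; no site clustering; contrast T1 minus the mean of T−3 to T−1.

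**Significance levels.** Single-step Šidák uses 1 − 0.95^(1/m): 0.0253 for m=2, 0.0127 for m=4, 0.0064 for m=8. For m=4, Holm-Šidák compares the ordered p-values with 1 − 0.95^(1/4), 1 − 0.95^(1/3), 1 − 0.95^(1/2) and 0.05, that is 0.0127, 0.0170, 0.0253 and 0.05. The first threshold is the same and the later ones are larger, so it rejects everything the single-step rule rejects, whatever the data.

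**The article's own figure.** In a three-period segmented model with levels and slopes and AR(1) 0.3, the standard error (SE) of a level change with 300 therapists is about 0.0706 SD. At d=0.5 and m=4: 0.5/0.0706 = 7.08 against a critical value of 2.49, so power is practically 100%. The >80% statement is met.

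**SE of the contrast used below.**
- Variance of the three-baseline mean: (3 + 2×(0.3 + 0.3 + 0.09))/9 = 0.4867.
- Mean covariance with T1: (0.3² + 0.3³ + 0.3⁴)/3 = 0.1251/3 = 0.0417.
- Variance of the difference: 1 + 0.4867 − 2×0.0417 = 1.4033.
- SE = √(1.4033/300) = 0.0684, close to the segmented-model value.

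Check at d=0.2, m=4: 0.2/0.0684 = 2.924, and Φ(2.924 − 2.491) = 66.8%.

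**Power per outcome** (400,000 simulated sets of test statistics per row, correlation 0.5):

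| m | d | Single-step | Step-down |
|---|---|---|---|
| 2 | 0.2 | 75% | 80% |
| 4 | 0.2 | 67% | 76% |
| 8 | 0.2 | 58% | 69% |
| 4 | 0.1 | 15% | 18% |
| 4 | 0.3 | 97% | 99% |
| 4 | 0.5 | 100% | 100% |

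For m=4 and d=0.2, correlations of 0.3 and 0.7 give gains of 10 and 8 points. The chance of at least one rejection is 91% under both rules.

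**A much larger SE.** Set the SE so that d=0.5 has exactly 80% power at m=4: 0.5/(2.491 + 0.842) = 0.150. Power per outcome then goes from 12% to 15% at d=0.2, 31% to 37% at d=0.3, and 80% to 87% at d=0.5. The gains are about 2, 6 and 7 points before rounding.

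**Family-wise error** (m=4, correlation 0.5). With no real effects it is 4.4% under both rules. With three large real effects it is 1.3% for single-step and 5.0% for step-down. Step-down uses the error allowance that single-step leaves unspent, and stays within 5%.

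**The case against.** The strongest reply is that nothing here is wrong. Šidák is valid, the 5% holds and the power statement stands; choosing one valid procedure over a more powerful one is close to preference. This is right as far as it goes, and it is why the point is offered as optional. A reader might infer from the numbers that the plan contains an error or that the study is underpowered. The article supports neither.

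Second, the phrase sits in a sample-size sentence, where planning at the strictest level is conservative, and the word single-step is not used. A separate analysis plan may settle the testing rule. This stands too: editing the sample-size sentence alone would not set the analysis rule. But Šidák is the only method the article names, and its ordinary meaning is single-step.

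Third, the size of the gain rests on unstated inputs, and d=0.2 lies near the largest gain under the smaller SE. This also stands. A reader might take d=0.2 as the effect the authors expect; the article says only minimal and modest. The chance that all four outcomes are significant rises more steeply (37% to 59% at d=0.2, m=4), but no part of the study requires all four, so that figure should not be used to size the benefit.

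Finally, single-step Šidák gives simple simultaneous intervals that agree with its tests, and step-down does not. That is a real trade-off. The article asks for Šidák intervals only for the effectiveness outcomes, so it does not prevent step-down testing of the therapist outcomes.

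**Conclusion.** The point holds as a cheap, optional improvement. That step-down never rejects less needs no assumption about effect size, SE or correlation. Both rules control the family-wise error under the same condition, independence or positive dependence of the tests.

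The size of the gain is uncertain. In the configurations tried it runs from nothing to about 11 points of per-outcome power, depending on family size, outcome correlation, SE and true effect. Site clustering and missing data, which the article's limitations section expects, would raise the SE and move the gain toward larger effects. The benefit is confined to second and later rejections.

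**What to change.** In the Data Analysis section of the implementation evaluation, state that the therapist-level outcomes are tested by step-down Holm-Šidák at a global 5%, naming the outcomes in the family or pointing to where the full analysis plan lists them. Cross-refer to that sentence from Number of Therapists. Keep single-step Šidák for any confidence intervals and leave the >80% power statement unchanged. Make the change before outcome data are analysed.

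The cost is one sentence and one cross-reference, with no extra data or participants. Because an outcome may be significant by step-down while its single-step interval includes zero, add one reporting sentence saying that the tests and the intervals use different procedures and that significance follows the step-down test.
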